### Primary outcome measures

Incidence of composite major complications [time frame: up to 30 days]:
Operative mortalitySecondary thoracotomyNew onset of postoperative renal failure requiring dialysis: increase in serum creatinine value ≥ 300% from baseline or an absolute serum creatinine ≥ 354 μmol/l with an increase ≥ 44 μmol/l from baseline (KDIGO stage 3) [17]. Any patient who received acute dialysis is put into this category. Patients who have received dialysis within 1 month prior to the surgery are not eligible for this endpointParaplegiaStroke/cerebrovascular accidentsLow cardiac output syndrome: cardiac index < 2.0 l min^−1^ m^−2^ for > 8 h after surgery, regardless of treatment [18]ReintubationSevere liver dysfunction: ALT level above 500 U/l or a total bilirubin above 3.0 mg/dl [19, 20]ECMO supportMultiple organ dysfunction syndrome (MODS)

Each of these outcomes will be analyzed as a secondary endpoint.

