### Secondary outcome measures

Changes in the levels of plasma inflammatory factors such as IL-6, IL-8, IL-10, IL-1β, and TNF-α [time frame: up to 3 days]Changes of plasma MIF levels during the perioperative period [time frame: up to 3 days]Changes of plasma CRP levels during the perioperative period [time frame: up to 3 days]Changes of the plasma II, VII, IX, X, XI, and XII levels during the perioperative period [time frame: 2 days]Changes of the plasma APTT, PT, FIB, FDP, and DDi levels during the perioperative period [time frame: 3 days]Total drainage within the first 24 h of surgery [time frame: 24 h]Incidence of postoperative acute kidney injury [time frame: up to 30 days]: increase in serum creatinine ≥ 150% or ≥ 26.5 μmol/l from baseline [13]Incidence of postoperative respiratory failure [time frame: up to 30 days]: uninterrupted postoperative mechanical ventilation for more than 48 h [10]Incidence of postoperative delirium [time frame: up to 30 days]: we will assess delirium once a day for a total of 3 times during the first 72 h after ICU admission, using standard delirium assessments (CAM or CAM-ICU). Before the CAM-ICU will be performed, a Richmond Agitation Sedation Scale (RASS) sore should be evaluated in advance [21]Incidence of postoperative liver injury [time frame: up to 30 days]: ALT level above 150 U/l [22]Incidence of postoperative myocardial infarction [time frame: up to 30 days]: a rise and/or fall of cTn values with at least 1 value above the 99th percentile upper reference limit and at least 1 of the following:
Symptoms of myocardial ischemiaNew ischemic ECG changesDevelopment of pathological Q wavesImaging evidence of new loss of viable myocardium or new regional wall motion abnormality in a pattern consistent with an ischemic etiologyIdentification of a coronary thrombus by angiography or autopsy (not for types 2 or 3 MIs) [23]

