### Data analysis

After completion of the trial, data analysis will be done by a certified statistician with SPSS20.0 (IBM, Chicago, IL, USA). Levels of inflammatory cytokines and coagulation parameters will be expressed as mean ± standard deviation or median (interquartile range). An independent *t* test or the Wilcoxon signed-rank test will be used to check if the data is within normal distribution before analysis. Categorical variables will be analyzed with chi-squared and Fisher’s exact tests.

The relative risk of primary and secondary outcomes in the hemoperfusion group and the control group will be compared using the multivariate logistic regression. Kaplan-Meier curves and log-rank analysis will be used to compare inter-group differences in primary and secondary outcomes. When comparing the changes in coagulation factor levels during the perioperative period, the effect of hemoperfusion on coagulation factors throughout the study will be assessed using repeated measures’ analysis of variance (ANOVA) and analysis of covariance (ANCOVA). When the *p* < 0.05, the result is considered statistically significant.

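### The 30-day composite falls under three tests with none named as deciding, and log-rank is assigned to secondary outcomes without restriction

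*Protocol article*

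**What the plan says.** The primary outcome is a yes/no quantity: "Incidence of composite major complications [time frame: up to 30 days"], with operative mortality among its ten components. The same section adds that "Each of these outcomes will be analyzed as a secondary endpoint".

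Three statements in Data analysis bear on it:

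- a general rule: "Categorical variables will be analyzed with chi-squared and Fisher’s exact tests";
- a sentence on the relative risk of primary and "secondary outcomes in the hemoperfusion group and the control group will be compared using the multivariate logistic regression", with no covariates named;
- "Kaplan-Meier curves and log-rank analysis will be used to compare inter-group differences in primary and secondary outcomes".

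The section ends with one significance rule: "When the *p* < 0.05, the result is considered statistically significant". It ranks none of the tests.

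Sample size calculation rests on two proportions, 33.3% (4 of 12) against 8.3% (1 of 12), with two-sided alpha 5% and power 80%. It gives 40 per group, raised to 44 for dropout.

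The Secondary outcome measures include cytokine, MIF, CRP and coagulation levels, 24-hour drainage, acute kidney injury, delirium and respiratory failure. The last is defined as "uninterrupted postoperative mechanical ventilation for more than 48 h".

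**The concern.** The trial has one primary hypothesis and a stated 5% two-sided error. The analysis text gives that hypothesis several tests and one threshold, and does not say which result settles it. If the comparison of proportions gave p = 0.06 and log-rank gave p = 0.04, the article would not tell a reader whether the trial had met its primary outcome. Choosing the deciding test after seeing the data is what pre-specification is meant to prevent.

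The log-rank sentence carries a second problem. Taken literally, it reaches outcomes that have no event time. It also reaches non-fatal events for which a patient who dies can no longer have the event. Operative mortality is a component of the composite, so the authors expect some deaths within the window.

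**Working it through.** **1. What the sample size rests on.** Inputs from Sample size calculation: p1 = 4/12 = 0.333, p2 = 1/12 = 0.083, alpha 0.05 two-sided, power 0.80. The pooled two-proportion formula is

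n = [1.960·√(2·p̄·q̄) + 0.842·√(p1q1 + p2q2)]² / (p1 − p2)²

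With p̄ = 5/24 = 0.2083, 2p̄q̄ = 0.3299 and p1q1 + p2q2 = 0.2222 + 0.0764 = 0.2986:

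n = (1.960 × 0.5743 + 0.842 × 0.5465)² / 0.0625 ≈ 40.2, so 41 when rounded up.

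The stated 40 is reproduced to within one patient, and power at 40 per group is 79.8%. Other forms give 38 (unpooled), 38 (arcsine) and 48 (continuity-corrected). The design therefore rests on a single comparison of two proportions. The article does not name the test.

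**2. How many tests reach the primary outcome.** Logistic regression and log-rank are assigned to it by name. Chi-squared/Fisher applies because a 30-day incidence is a categorical variable. That makes two explicit tests and one by the general rule, all judged at p < 0.05.

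**3. Error rate if any one of the three suffices.** If the tests were independent, the chance of at least one false positive would be 1 − 0.95³ = 0.143. They use the same data and are strongly correlated, so this has to be simulated. The base run used 40 per arm, no treatment effect, two standard-normal prognostic covariates (log-odds 0.5 each), exponential event times with mean 5 days, complete 30-day follow-up and 10,000 trials. The covariates and the event-time model are assumptions; the article gives neither.

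| Null event rate | Chi-squared | Logistic | Log-rank | Any of three |
|---|---|---|---|---|
| 33% | 4.97% | 5.09% | 5.31% | 7.1% |
| 21% | 4.85% | 4.86% | 4.78% | 6.4% |

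Fisher's test alone ran at 2.8% in both settings and added nothing to the last column.

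Varying the covariates at 33% events (4,000 or 6,000 trials per setting):

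| Assumed covariates | Any of three |
|---|---|
| none | 5.6% |
| two, log-odds 0.5 | 7.1–7.2% |
| six, log-odds 0 or 0.3 | 7.6% |
| six, log-odds 0.3 | 7.9% |
| six, log-odds 0.5 | 7.6% and 8.6% (separate runs) |
| six, log-odds 0.7 | 9.1% |

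The Monte Carlo standard error at 7% is √(0.07 × 0.93/4,000) ≈ 0.4 percentage points, so these figures are best read as a range. Allowing only chi-squared or log-rank gave 5.4–5.8%. Most of the excess therefore comes from the adjusted model.

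At the design rates (33.3% against 8.3%, two covariates, 3,000 trials), the chance of significance was 80.6% for chi-squared, 79.1% for logistic, 80.2% for log-rank, 73.4% for Fisher and 84.2% for at least one.

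**4. Secondary outcomes against log-rank.** Biomarker levels and 24-hour drainage are measurements with no event time. Ventilation beyond 48 hours is a status settled at one fixed time, so a curve adds nothing to a proportion. Dialysis, stroke and reintubation (components) and delirium and acute kidney injury (separate secondary outcomes) are non-fatal events that death can prevent.

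**5. Effect of censoring deaths.** Write H1 and H2 for the cumulative cause-specific hazards of the event and of death, and h1 for the hazard of the event. The true 30-day incidence is ∫h1·exp(−H1 − H2)dt. One minus Kaplan-Meier with deaths censored estimates ∫h1·exp(−H1)dt. Since exp(−H1 − H2) ≤ exp(−H1), the second is never smaller, and it is larger whenever deaths precede possible events. The log-rank test on such data compares the event hazard among those still alive, which is a different question from 30-day incidence. The article gives no mortality rate by arm, so the gap cannot be computed. For the composite itself death is an event and does not compete.

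**The case against.** The strongest reply has four parts.

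- **The deciding analysis may be named elsewhere.** A statistical analysis plan or full protocol commonly does this, and neither is shown. That would answer a pure omission. Here the article positively assigns overlapping methods to the primary outcome and applies one threshold to each, so another document would have to narrow published text. The point stands, as a matter of wording.
- **No any-of-three rule is stated.** This is correct. A reader might infer that the article declares success on any one p-value, or that the error is near 14%, or exactly some figure such as 8.2%. It states no such rule. The 14% ignores correlation, and 8.2% is one six-covariate result within an assumption-dependent range. The inflation is conditional and modest.
- **Log-rank on cytokines is an implausible reading.** A reader might infer that log-rank is ordered for every secondary outcome. The text says neither all nor every. The parallel sentence on relative risk fits only events, levels are summarised by means or medians, and coagulation factors get repeated-measures analyses. What stands is that the sentence carries no restriction and needs one.
- **Censoring of deaths is not stated.** This is also correct. It is the ordinary Kaplan-Meier default, and the article mentions no competing-risk method. A claim that one arm would be favoured, or by how much, goes beyond the documents.

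A reader might also infer that the sample size prescribes chi-squared. It supports only a comparison of proportions.

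**Conclusion.** The point holds in this form. The binary 30-day composite is assigned logistic regression and log-rank by name and chi-squared/Fisher by the general rule, with p < 0.05 for each and no deciding test. If any one of them could support a claim of success, the two-sided type I error is roughly 5.5% to 9% against the stated 5%. This rests on 40 per arm, 33% events and assumed covariates and event times. Each test taken alone is at or below about 5%, so the fault lies in the missing hierarchy and not in any one method.

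The unrestricted log-rank sentence does not fit biomarker levels or drainage. For non-fatal events, Kaplan-Meier with deaths censored would overstate incidence by an amount the article does not allow to be quantified. That part concerns secondary outcomes only.

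**What to change.** In Data analysis:

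1. Name one deciding primary analysis: the comparison of 30-day composite proportions between arms, with risk difference and 95% confidence interval. This matches the 33.3% against 8.3% basis of the sample size. State in advance whether chi-squared or Fisher's exact test is used, since Fisher gave about 73% power in the simulation against about 81% for chi-squared.
2. Label the adjusted logistic model, with its covariates listed, and log-rank for time to first composite event as supportive.
3. Limit Kaplan-Meier and log-rank to the composite and all-cause death.
4. Report non-fatal events as 30-day proportions, or as cumulative incidence with death as a competing event.

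The cost is wording only, with no new data and no change in sample size. The downside is that two of the three primary-outcome p-values become supportive and cannot carry the claim.

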**Discussion:**

In the current trial, hemoperfusion will be applied in patients undergoing CPB and DHCA for repair of the aorta involving the aortic arch. This trial aims to test the safety and efficacy of our hemoperfusion device (HA380) in such settings. Upon completion of the trial, we will determine if HA380 is effective in reducing perioperative proinflammatory cytokine levels. Further, we will also verify if reduction in the proinflammatory cytokine levels, if present, translates to improvement in patient outcomes.

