### Blood sample collection and detection

During the perioperative period, plasma inflammatory factors levels will be measured at the following time points: before operation (T0), CPB initiation (T1), lowest intraoperative temperature (T2), end of CPB (T3), end of the operation (T4), 24 h after completion of the procedure (T5), 48 h after completion of the procedure (T6), and 72 h after completion of the procedure (T7).

Parameters of coagulation including plasma-activated partial thromboplastin time (APTT), prothrombin time (PT), fibrinogen (FIB), fibrinogen degradation product (FDP), and d-dimer (DDi) levels will be measured at the following time points: before operation, 24 h after completion of the procedure (POD 1), 48 h after completion of the procedure (POD 2), and 72 h after completion of the procedure (POD 3).

Similarly, levels of coagulation factors including II, VII, IX, X, XI, and XII will be measured at the following time points: before operation, end of CPB, end of the operation, 24 h after completion of the procedure (POD 1), and 48 h after completion of the procedure (POD 2).

Measurement of inflammatory cytokines levels: blood samples are collected through radial artery catheterization. The first 5 ml will be discarded when sampling. Following collection, blood samples are immediately centrifuged at 3000 rpm for 15 min at 4 °C. The plasma yielded will be stored in the − 80 °C refrigerator till the time of measurements. Enzyme-linked immunosorbent assay (ELISA) is used for the measurement of inflammatory cytokines.

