### Sample size calculation

Primarily, we expect the incidence of composite major complications to be decreased in the HA380 hemoperfusion group (intervention group) compared with the control group. The sample size was calculated with our preliminary results from the pilot study, in which the primary outcome was defined as the incidence of composite major complications. In this study, we included 24 patients (*n* = 12 in each group), in which 8.3% (1 out of 12) of the patients assigned to the intervention group underwent CRRT due to severe postoperative renal failure. In contrast, 33.3% (4 out of 12) patients had either one of the following outcomes: death, secondary thoracotomy, and renal failure requiring dialysis. Assuming a two-sided type I error probability (α) of 5% and type II error probability (β) of 20%, forty patients are needed in each group. Suppose 10% of patients drop out either due to changes in surgical methods or lost in follow-up, a minimum number of 44 patients in each group are needed in order to achieve statistical significance.

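### No single cytokine comparison is fixed to decide the trial's stated main purpose, while every p<0.05 counts as significant

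*Protocol article*

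**What the plan says.** All references are to the protocol article.

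- **Purpose.** Objective and hypothesis gives as the main purpose finding out whether pro- and anti-inflammatory cytokine levels differ between the arms. The Discussion paragraph of the abstract promises a verdict: "we will determine if HA380 is effective in reducing perioperative proinflammatory cytokine levels". The closing part of the main Discussion repeats this aim.
- **Markers.** Secondary outcome measures lists "Changes in the levels of plasma inflammatory factors such as IL-6, IL-8, IL-10, IL-1β, and TNF-α", then MIF and CRP as separate items. That is five named cytokines in an open list, or seven inflammatory markers in all.
- **Times.** Blood sample collection and detection says that "plasma inflammatory factors levels will be measured at the following time points" and lists T0 to T7: one preoperative sample and seven later ones.
- **Analysis.** Data analysis describes cytokine and coagulation levels by mean or median. It mentions a t test or Wilcoxon signed-rank test, but as a check of normality. It names repeated-measures ANOVA and ANCOVA for coagulation factors only. Logistic regression and Kaplan-Meier methods are given for primary and secondary outcomes in general, but they do not suit serial continuous levels. The section ends: "When the *p* < 0.05, the result is considered statistically significant".
- **Primary outcome.** The composite of major complications is the one declared primary outcome, and the sample size is built on it.

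**The concern.** The article commits the trial to a yes-or-no statement about cytokines but does not say which marker, time or summary decides it. The one rule it does state treats every p-value below 0.05 alike. The longitudinal analysis that would reduce each marker to one comparison goes to the coagulation factors and not to the markers that carry the main purpose. Within the published text, the marker and the summary could be chosen after the results are known, and one nominally significant marker could be reported as showing that the device changes cytokines. At stake is the credibility of the trial's mechanistic conclusion, because an inert device would produce such a finding well above 5% of the time.

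**Working it through.** **1. The plan's own figure.** Inputs from Sample size calculation: "8.3% (1 out of 12) of the patients assigned to the intervention group underwent CRRT"; "33.3% (4 out of 12) patients had either one of the following outcomes"; two-sided alpha 5%; "type II error probability (β) of 20%, forty patients are needed in each group". With p1 = 4/12, p2 = 1/12 and mean p = 0.2083:

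n = [1.96·√(2·0.2083·0.7917) + 0.8416·√(0.3333·0.6667 + 0.0833·0.9167)]² / 0.25² = (1.1257 + 0.4599)² / 0.0625 = 40.2.

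The stated 40 per group is reproduced, and 40 × 1.1 = 44 matches the inflated figure. This calculation concerns only the composite. The article states no error rate for the cytokine question.

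**2. One test per marker** (for example, one longitudinal group test each). With no device effect and independent markers, the chance of at least one p<0.05 is 1 − 0.95^m:

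- m = 5: 1 − 0.95^5 = 22.6%
- m = 7: 1 − 0.95^7 = 30.2%

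Simulating jointly normal null test statistics (100,000 draws) with an assumed correlation of 0.5 between markers gives about 18% and 23%. At 0.7 it gives about 15% and 18%.

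**3. A separate test at each time** (an inference; the text does not state it). Seven post-baseline times give 5 × 7 = 35 or 7 × 7 = 49 tests, assuming MIF and CRP follow the same schedule. If independent: 1 − 0.95^35 = 83.4% and 1 − 0.95^49 = 91.9%. With an assumed equal correlation r between markers and between times (same simulation method):

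| r | 35 tests | 49 tests |
|---|---|---|
| 0 | 83.4% | 91.9% |
| 0.3 | 76.6% | 85.8% |
| 0.5 | 64.2% | 73.4% |
| 0.6 | 55.2% | 63.6% |
| 0.7 | 45.0% | 51.5% |
| 0.8 | 33.5% | 37.9% |
| 0.9 | 21.7% | 23.8% |

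The 50% line is crossed near r = 0.65 for 35 tests and near r = 0.7 for 49.

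**4. The narrower claim in the abstract: a fall in proinflammatory cytokines.** Leave out IL-10, which the Discussion calls anti-inflammatory, and four listed cytokines remain. Take the six times from T2, since T1 is the start of bypass: 4 × 6 = 24 tests, each with a 2.5% chance of a significant result in the favourable direction. If independent, 1 − 0.975^24 = 45.5%, or about 46%. It is about 36% with assumed correlations of 0.3 between markers and 0.5 between adjacent times, and about 28% with 0.5 and 0.7. Adding T1 gives 28 tests and 1 − 0.975^28 = 50.8%, but only under full independence.

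**The case against.** The strongest reply is that the article never says arms will be compared marker by marker and time by time. The t test sentence is badly worded, but it is not a plan of that kind. A condensed article may also leave the longitudinal model, log transformation and any multiplicity rule for secondary markers to a fuller protocol or SAP that is not shown. Cytokines are listed as secondary, and the single primary test is sound in this respect.

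Much of this stands. A reader might infer that a trial of an inert device would find a significant cytokine difference more often than not. The documents do not support that. It requires per-time testing, which is not stated, and weak to moderate correlation, which is not given. It also fails for the abstract's directional claim, where the chance is at most about 46% over the six times from T2.

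The appeal to an unseen plan does not answer everything. The point rests on what the article does state: a cytokine main purpose, a promised verdict, an open marker list, a longitudinal analysis assigned to a different group of markers, and a general significance rule. Nothing labels the cytokine results exploratory. Even on the favourable reading of one test per marker, the error rate for finding some marker different is several times 5%.

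**Conclusion.** The point holds in limited form. The article fixes no single comparison for its stated main purpose, and its general threshold leaves the chance of a false cytokine finding well above 5%. With one test per marker the chance is about 18% to 30%, for five to seven markers and correlation from 0 to 0.5. If every post-baseline time were tested it would be about 22% to 92% for correlation from 0.9 down to 0. All the correlations are assumptions, so no one figure in these ranges can be called the trial's actual error rate. The primary composite comparison and its sample size are not touched. This is worth correcting because the cytokine conclusion is a headline claim, but it does not threaten the main efficacy test.

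**What to change.** In Data analysis, extend the longitudinal analysis to the inflammatory markers: for each, one between-arm contrast over the post-exposure samples, adjusted for T0, on the log scale if the values are skewed. In Secondary outcome measures, replace the open list with a closed one. Before unblinding, name the one cytokine whose contrast decides the claim in the abstract, tested at two-sided 0.05. IL-6 is a natural candidate because the Discussion gives it its own rationale, but that section also discusses IL-10 and MIF, so the choice is the sponsor's. Adjust the other markers by Holm's method or report them as descriptive. Present comparisons at single times as estimates with confidence intervals, without significance claims.

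The cost is wording, since the samples and assays are already planned. The small downside is that an isolated significant marker or time point could no longer be claimed as evidence that the device lowers cytokines.
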